**6 Statistical analysis**

**6.1 Calculation of sample size**

This study uses the objective response rate (ORR) as the primary end point. This single-arm study requires 56 eligible patients. Considering a 10% dropout rate, a total of 63 patients will be enrolled.

The research hypothesis is based on Checkmate 017 and Checkmate 057 study, which reported an ORR of 20%. If the ORR of the experimental treatment in this study is 20%, it is not worthy of further study. But if the ORR of the experimental treatment in this study is 38%, the study is considered successful. The purpose of this study is to distinguish ORR between 20% and 38%. The statistical assumptions are: the null hypothesis ORR<=20%, and the opposite hypothesis ORR>=38%. If 17 or more of the 56 eligible patients are CR or PR, this study is deemed successful and is worthy of further study. With a one-sided type one error rate (alpha) equal to 0.0432, this study has at least 90% statistical power to reject the null hypothesis.

**6.2 Safety Run-in**

In this study, dose-limiting toxicity (DLT) includes the following three conditions and asymptomatic biochemical abnormalities without clinical significance are not included:

(1) Grade 3 toxicity lasts for more than 7 consecutive days;

(2) Grade 4 toxicity

(3) Grade 5 toxicity that could not be ruled out the association with the trial treatment

To prevent the experimental treatment from causing excessive toxicity to patients, we will monitor the toxicity of the first 20 patients receiving the experimental treatment. Within 30 days after the first dose of sintilimab and GM-CSF, if 7 or more of these 20 patients develop any of the pre-defined DLTs, enrollment will be suspended immediately. After reviewing the data and other details, the research team will decide whether to revise the trial's treatment plan to reduce the incidence of DLT or to terminate the entire trial. This safety run-in phase of the trial has the following statistical characteristics. In this treatment scenario, it is assumed that a DLT rate of 25% or lower is acceptable, while a DLT rate of 45% or higher is not acceptable. When the DLT rate is equal to 25%, the probability of termination of the test in the Run-in phase is 0.1018; when the DLT rate is equal to 30%, the probability of termination of the test in the Run-in phase is 0.7480. In addition, if there are more than 4 deaths caused by treatment in the first 20 treated patients within the first 60 days of treatment, the trial will be stopped immediately and investigation will be carried out.

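### The numeric DLT trigger in section 6.2 ends at patient 20 of 63; continuing the same count with review pauses near 30, 40 and 50 patients would be a cheap improvement

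*Protocol*

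**What the plan says.** Section 6.2 of the protocol (Safety Run-in) states its purpose as follows: "To prevent the experimental treatment from causing excessive toxicity to patients". It then sets who is covered: "we will monitor the toxicity of the first 20 patients receiving the experimental treatment". It applies a 30-day DLT window, counted from the first dose of sintilimab and GM-CSF, and suspends enrollment "if 7 or more of these 20 patients develop any of the pre-defined DLTs". It defines its targets: "a DLT rate of 25% or lower is acceptable, while a DLT rate of 45% or higher is not acceptable". After a suspension the research team may either revise the treatment "to reduce the incidence of DLT or to terminate the entire trial". A second rule in the same section, based on more than four treatment-caused deaths within 60 days, is also confined to the first 20 treated patients.

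Section 6.1 sets the size of the trial: "a total of 63 patients will be enrolled". Section 6.3 expects 4 to 5 patients per month.

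After the run-in, the protocol keeps rules for individual patients (sintilimab suspension and discontinuation in 5.2.2, GM-CSF in 5.3), withdrawal at the investigator's judgment (3.3), and SAE reporting within 24 hours to the sponsor, ethics committee and regulators (7.5). Section 6.6 summarizes adverse events descriptively. None of these sections ties a pause in enrollment to a count.

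**The concern.** The purpose in section 6.2 is to protect patients from excessive toxicity, and the section names a DLT rate at which the treatment is not acceptable. The only count that acts on that rate stops after 20 patients. Most patients enter later: 63 - 20 = 43. The wording has to be up to 43, because section 6.2 does not hold accrual while the 30-day window closes. At 4 to 5 patients per month, about that many may enroll before the run-in count is final.

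A run-in of 20 will sometimes pass a treatment that is too toxic. When it does, no agreed number of later DLTs prompts the research team to stop and look. Continuing the same count would supply one. The point concerns 30-day DLTs only, not late toxicity.

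**Working it through.** **Inputs.** Trigger 7 or more of 20, acceptable rate 25%, unacceptable rate 45%, and printed stopping probabilities 0.1018 and 0.7480 (section 6.2). Maximum of 63 patients (6.1). Accrual of 4 to 5 per month (6.3). The later looks at 30, 40 and 50 patients are my illustration.

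**Step 1: the plan's own figures.** With X the number of DLTs in 20 patients, binomial with rate p:

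| Rule | p = 25% | p = 30% | p = 45% |
| --- | --- | --- | --- |
| P(X ≥ 7) | 0.2142 | 0.3920 | 0.8701 |
| P(X ≥ 8) | 0.1018 | 0.2277 | 0.7480 |

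The printed 0.1018 (given for 25%) and 0.7480 (given for 30%) do not belong to the written rule. They are P(X ≥ 8) at 25% and at 45%. That mismatch is a separate matter, but it means both starting rules have to be carried here.

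**Step 2: what the run-in misses.** At 45% the run-in fails to pause with probability 1 - 0.8701 = 0.130 under 7/20, or 1 - 0.7480 = 0.252 under 8/20.

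**Step 3: add looks.** Pause if cumulative DLTs reach 12 at 30 patients, 15 at 40 or 18 at 50. Exact recursion: carry forward the distribution of the count among trials not yet paused, add the binomial count from the next 10 patients, and remove the mass at or above the boundary.

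| Probability of ever pausing | 25% | 30% | 45% |
| --- | --- | --- | --- |
| 7/20 alone | 0.214 | 0.392 | 0.870 |
| 7/20 + looks | 0.235 | 0.456 | 0.962 |
| 8/20 alone | 0.102 | 0.228 | 0.748 |
| 8/20 + looks | 0.142 | 0.350 | 0.949 |

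**Step 4: patients spared at 45%.** If a pause ends enrollment, the saving is the sum over looks of (probability of pausing there) × (63 - n).

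- Under 7/20 the pause probabilities at 30, 40 and 50 are 0.0236, 0.0407 and 0.0279. Saving: 0.0236 × 33 + 0.0407 × 23 + 0.0279 × 13 = 2.08 patients (mean treated 25.6 to 23.5). In DLTs: 2.08 × 0.45 = 0.94.
- If 4 more patients enroll while each look's window closes (an assumption, from 4 to 5 per month and 30 days), the multipliers become 29, 19 and 9. Saving: 1.71 patients, or 0.77 with a DLT.
- Under 8/20 the pause probabilities are 0.0841, 0.0748 and 0.0425. Saving: 5.05 patients, or 4.24 with the lag.

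**Step 5: where the gain arises under 7/20.** The looks at 40 and 50 supply (0.0407 + 0.0279) / 0.0922 = 74% of the added pauses. The first look contributes little because its boundary, 12/30 = 40%, is looser than the run-in trigger, 7/20 = 35%. A trial that passed with at most 6 DLTs needs at least 6 more in the next 10 patients to reach it. The set fits 8/20 = 40% better.

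**Step 6: the death rule.** At an assumed 5% treatment mortality, P(5 or more deaths) is 0.003 in 20 patients and 0.207 in 63.

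**The case against.** The strongest reply is that a run-in limited to the first patients is ordinary practice, and that ongoing safety thresholds may sit in a monitoring plan or SAP that is not at hand. This stands to the extent that nothing in section 6.2 is wrong on this point. But 6.2 is where the protocol places its enrollment-suspending count, and it confines that count to 20 patients.

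Second, the benefit under the written rule is small: about 2 patients and less than one DLT per trial, at a rate nothing in the protocol makes likely. The background reports no treatment-related dose reduction or interruption among 41 patients given radiotherapy with GM-CSF, although that study did not test the triple combination. This stands.

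Third, the extra pauses at 30% are not trivial (39% to 46% under 7/20, 23% to 35% under 8/20). This also stands, although 30% lies between the plan's two limits and a pause leads to review.

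Two stronger readings are tempting. A reader might infer that patients 21 to 63 are left without safety protection. The documents do not support that: sections 3.3, 5.2.2, 5.3 and 7.5 apply to all patients, and nothing prevents a pause on that information. A reader might also take the share of wrongly passed trials caught later under 7/20, 0.0922 / 0.1299 = 71%, as the size of the benefit. It overstates it, because passing is uncommon at 45% and about three quarters of those pauses come when 40 or 50 patients are already enrolled.

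**Conclusion.** The point holds as a low-cost improvement to consider. Section 6.2 has no DLT count after patient 20, and adding one improves detection of the plan's own unacceptable rate. Its size depends on the unsettled boundary. Under the written 7/20 it is modest: 9 points more at 45%, for 2 points at 25% and 6 at 30%. Under 8/20 it is worth more: 20 points at 45%, for 4 and 12.

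The figures assume independent DLTs at a constant rate and complete 30-day data at each look. The patient savings also treat every pause as the end of enrollment, so they are upper-end values: section 6.2 lets the team revise the treatment and continue.

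**What to change.** First settle whether the run-in boundary is 7 or 8 of 20. Then continue the same 30-day DLT count in section 6.2, with the research team pausing enrollment for review at boundaries near 30, 40 and 50 patients, and print the operating characteristics of the full rule at 25%, 30% and 45%.

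- **If 8/20:** 12/30, 15/40 and 18/50 are suitable.
- **If 7/20:** reset the first look. For example, 11/30, 14/40 and 18/50 (37%, 35% and 36%) give pause probabilities of 0.255, 0.489 and 0.969 at 25%, 30% and 45%. That is about 2.6 fewer patients treated at 45% (2.2 with the lag), for 4 more points at 25% and 10 at 30%. If those extra pauses are unwelcome, 12/30, 16/40 and 19/50 give 0.224, 0.427 and 0.946 and save 1.7 patients (1.4 with the lag), but keep the loose first look.

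Do not carry the death rule forward unchanged. With a fixed count of five and a growing denominator, it would stop about one trial in five at 5% treatment mortality.

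The cost is a short amendment, with no extra patients, visits or committee. Each look does need adjudication beyond tabulated grades and dates. The DLT definition requires judgment on clinical significance ("asymptomatic biochemical abnormalities without clinical significance are not included") and on relatedness ("Grade 5 toxicity that could not be ruled out the association with the trial treatment"). The team already makes these judgments for the first 20 patients.

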**5 Treatment**

The combination of SBRT with sintilimab and GM-CSF is applied. One lesion (primary or metastatic lesion) is selected for SBRT, with the dose of 24Gy/3Fx. Within Two weeks after SBRT is completed, Sintilimab and GM-CSF treatment are initiated and used in combination, with the date recorded as d1. GM-CSF is continuously used for 14 days (d1-d14) at the dose of 125 μg/m^2^. Sintilimab is administrated at the dose of 200 mg/time once every 3 weeks from d1 (d21n +1, n≥0), 35 cycles in total (2 years), or until the investigator deems that the patient needs to be discontinued due to treatment-related toxicity or disease progression. The overall response rate and toxicity were assessed periodically.

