**5.1 SBRT**

One primary or metastatic lesion with a size of 1-5 cm, a clear boundary, little influence on surrounding normal tissues and no previous irradiation is selected and performed SBRT. The total dose of each lesion is 24 Gy/3 Fx (8 Gy/Fx). Each lesion is irradiated once a day for 3 consecutive days. Taking into account the failure of the radiotherapy machine and other factors, it is allowed to complete 3 fractions within 5 days.

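### The run-in DLT count opens at the first drug dose, so non-fatal DLTs confined to the SBRT period, and DLTs in patients who never start drug, miss the 7-of-20 rule

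*Protocol*

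**What the plan says.** Protocol section 6.2 gives the purpose of the run-in as "To prevent the experimental treatment from causing excessive toxicity to patients" and states that "we will monitor the toxicity of the first 20 patients receiving the experimental treatment". Section 5 defines that treatment: "The combination of SBRT with sintilimab and GM-CSF is applied". SBRT comes first.

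Section 6.2 lists three DLT criteria: grade 3 toxicity for more than 7 consecutive days, grade 4 toxicity, and grade 5 toxicity whose link to the trial treatment cannot be ruled out. Asymptomatic biochemical abnormalities without clinical significance are set aside. The stopping rule then counts patients with a DLT as follows: "Within 30 days after the first dose of sintilimab and GM-CSF, if 7 or more of these 20 patients develop" one of these. A second rule in the same paragraph stops the trial for more than 4 treatment-caused deaths among the first 20 treated patients "within the first 60 days of treatment".

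On timing, section 5.1 plans three consecutive daily fractions, but "it is allowed to complete 3 fractions within 5 days". Section 5 then says "Within Two weeks after SBRT is completed, Sintilimab and GM-CSF treatment are initiated and used in combination, with the date recorded as d1". Sections 5.2 and 5.3 instead put d1 on the second day after SBRT is completed.

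**The concern.** The regimen being monitored and the window in which its toxicity counts do not match. SBRT is one of the three components and is given first, yet the SBRT days and the gap before d1 lie outside the DLT window. Nothing elsewhere in the protocol extends the count back to the first fraction.

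A patient who starts SBRT and never reaches d1 has no DLT window at all, and section 6.2 does not say whether that patient is one of the 20. The two rules for the same 20 patients may also run from different dates, because the start of treatment in the death rule could be read as the first fraction.

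Any effect on the DLT rule goes one way. Leaving out early DLTs can only lower the observed rate, and so makes suspension of enrollment less likely when the whole regimen is too toxic.

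**Working it through.** **1. Length of the uncounted period**

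- SBRT course (5.1): 3 days, at most 5.
- Gap under 5.2 and 5.3 (d1 on the second day after SBRT): about 1 day between the last fraction and d1. Total before d1: 3 + 1 = 4 to 5 + 1 = 6 days.
- Gap under section 5 (within two weeks): up to 14 days. Total: up to about 5 + 14 = 19 days, beside a 30-day window.

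**2. Which DLTs can be missed**

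| Event | d1 on the second day after SBRT | d1 up to two weeks after SBRT |
|---|---|---|
| Grade 4, starts and resolves before d1 | Missed | Missed |
| Grade 3 for over 7 days | Starts at most about 6 days before d1, so passes 7 days only after d1 and meets the criterion inside the window | Can meet the criterion and resolve before d1: missed |
| Any DLT-grade event in a patient who never reaches d1 | No window | No window |
| Event that starts before d1 and continues past it | Not addressed in 6.2 | Not addressed in 6.2 |
| Treatment-caused death before d1 | Outside the DLT count; may fall under the 60-day death rule | Same |

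**3. The plan's own figures**

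Section 6.2 prints suspension probabilities of 0.1018 at a DLT rate of 25% and 0.7480 at a rate printed as 30%. With X ~ Binomial(20, p):

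| p | P(X ≥ 7) | P(X ≥ 8) |
|---|---|---|
| 0.25 | 0.2142 | 0.1018 |
| 0.30 | 0.3920 | 0.2277 |
| 0.45 | 0.8701 | 0.7480 |

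The printed values are those of an 8-or-more rule at 25% and 45%. They do not match the stated cut-off of 7. That is a separate error; it neither supports nor weakens this point. The steps below use the cut-off as stated.

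**4. Illustration of the loss**

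Assume the unacceptable rate of 45% is a whole-regimen rate, and that a share s of DLTs falls before d1 and goes uncounted while those patients stay among the 20. The counted rate is 0.45 × (1 − s). The shares are assumptions; the protocol gives no pre-d1 DLT rate.

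| s | Counted rate | P(X ≥ 7) |
|---|---|---|
| 0 | 0.450 | 0.870 |
| 5% | 0.4275 | 0.822 |
| 10% | 0.405 | 0.764 |
| 20% | 0.360 | 0.620 |

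If instead all those patients fail to reach d1 and are replaced among the 20, the counted rate is 0.45(1 − s)/(1 − 0.45s). That gives 0.4373, 0.4241 and 0.3956, with P(X ≥ 7) of 0.844, 0.814 and 0.737. The loss is smaller but in the same direction.

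**5. The opposite assumption**

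If 25% and 45% were meant for the 30-day window alone, the present rule works as designed for that window. Adding an independent pre-d1 DLT probability q gives an overall rate of 1 − (1 − p)(1 − q):

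| q (assumed) | Overall rate from p = 0.25 | P(X ≥ 7) | Overall rate from p = 0.45 | P(X ≥ 7) |
|---|---|---|---|---|
| 0 | 0.2500 | 0.2142 | 0.4500 | 0.8701 |
| 1% | 0.2575 | 0.2384 | 0.4555 | 0.8802 |
| 2% | 0.2650 | 0.2636 | 0.4610 | 0.8898 |
| 5% | 0.2875 | 0.3446 | 0.4775 | 0.9152 |

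**The case against.** The strongest reply is that section 6.2 fixes one clear clock, and that starting it when the three components first come together is a defensible way to observe the toxicity of the combination. Two rules for different events may also use different clocks without contradicting each other. This stands in part: the text is not internally false. It does not explain why a rule meant to protect against the experimental treatment leaves out that treatment's first component.

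Several stronger readings are tempting but not supported:

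- **That toxicity before d1 goes unmonitored.** Sections 7.1 and 7.4.1 collect AEs from consent, section 7.5 requires SAE reports within 24 hours from consent, and Table 1 has an AE assessment in the SBRT column. Only the DLT tally is affected.
- **That the DLT rule is the only formal protection.** The 60-day death rule is also a stopping rule and may include SBRT days.
- **That prolonged grade 3 events are missed whatever interval applies.** With d1 on the second day after SBRT, such an event passes 7 days only after d1.
- **That patients who receive SBRT only are dropped from the 20.** Section 6.2 is silent. Section 3.3 keeps withdrawn patients who received protocol treatment in the safety analysis.
- **That a given loss of power is established.** The pre-d1 shares are assumed, and the 25% and 45% rates may have been meant for the 30-day window.

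It is also right that treating every toxicity-related failure to start drug as a DLT would create a fourth criterion. The fix below does not do that.

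**Conclusion.** The point holds in a limited form. As written, the formal rule for non-fatal toxicity omits grade 4 events that start and resolve before d1, and DLT-grade toxicity in patients who never reach d1. It can also omit prolonged grade 3 events if the two-week interval applies. The first two gaps exist under either SBRT-to-d1 interval.

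The size is unknown. If 45% is a whole-regimen rate and the affected patients stay among the 20, an uncounted share of 5% to 20% lowers the suspension probability from 0.870 to between 0.822 and 0.620. If pre-d1 DLTs are rare, which the short interval makes more likely, the effect is small. The change is worth making because the omission can only lower the DLT count and the correction is cheap, not because a large bias has been shown.

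**What to change.** In section 6.2:

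1. Count DLTs under the three existing criteria from the first SBRT fraction to 30 days after the first dose of sintilimab and GM-CSF.
2. Define the 20 as the first 20 patients to start SBRT. Follow those who never start drug for a stated period, and count them as a DLT only if they meet an existing criterion.
3. State that the 60-day death rule runs from the same first-fraction date.
4. State that the 25% and 45% rates refer to this window, and give the suspension probabilities for it.

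Sections 5, 5.2 and 5.3 disagree on the SBRT-to-d1 interval and must be reconciled separately. This fix does not depend on how that is settled.

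Cost: an amendment to one paragraph. Table 1 already schedules AE assessment in the SBRT column, though follow-up of patients who never start drug must be written in. The DLT count may rise a little, and with it the chance of suspension: at 25% inside the present window, from 0.2142 to 0.2384 or 0.2636 if an assumed 1% or 2% of patients have a pre-d1 DLT. At an assumed 5% it would be 0.3446, but the whole-regimen rate would then be 28.75%, above the 25% that the protocol calls acceptable.

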In summary, the combined application of SBRT, sintilimab, and GM-CSF may enhance the effect of immunotherapy, thereby improving the clinical efficacy in advanced NSCLC. So far, there have been no prospective studies to confirm this scientific hypothesis, as well as the clinical value of the combination therapy. Therefore, we plan to carry out a phase II study of SBRT combined with sintilimab and GM-CSF in the treatment of advanced NSCLC, attempting to explore the feasibility of this triple therapy which mechanically could enhance anti-tumor immune response through promotion of both innate and adaptive immune processes.

1. Study objectives

To explore the safety and preliminary efficacy of SBRT combined with sintilimab and GM-CSF in stage IV NSCLC patients without driver mutations such as EGFR, ALK, and ROS1.

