**6.3 Patient recruitment**

Assuming that the monthly recruitment rate is 4-5 patients, this trial is expected to complete the recruitment of patients 13-16 months after the start of the study. The last patient was followed up for another 25 months after enrollment.

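### The safety run-in has a single DLT count (7 of the first 20) and no boundary at a smaller number of patients, and its printed probabilities belong to a different count

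*Protocol*

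**What the plan says.** Section 6.2 announces that "we will monitor the toxicity of the first 20 patients receiving the experimental treatment" and sets the observation window: "Within 30 days after the first dose of sintilimab and GM-CSF". The trigger is a count: "if 7 or more of these 20 patients develop any of the pre-defined DLTs, enrollment will be suspended immediately". The research team then looks at the data and chooses between revising the treatment plan and ending the trial. Resuming unchanged is not among the named outcomes.

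The section gives its design rates, "it is assumed that a DLT rate of 25% or lower is acceptable, while a DLT rate of 45% or higher is not acceptable", and two operating characteristics: "When the DLT rate is equal to 25%, the probability of termination of the test in the Run-in phase is 0.1018" and "when the DLT rate is equal to 30%, the probability of termination of the test in the Run-in phase is 0.7480".

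The only other run-in trigger is more than four treatment-caused deaths among the first 20 patients within 60 days. Section 6.2 contains no DLT boundary at fewer than 20 patients, no staggered entry and no hold on accrual while earlier patients are observed. Section 6.3 plans continuous entry: "Assuming that the monthly recruitment rate is 4-5 patients".

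**The concern.** A run-in is meant to react early if toxicity is clearly excessive. This one cannot react before the seventh DLT, however few patients have produced the first six. Six of six, or six of ten, is well above the 45% that the protocol calls unacceptable, yet the DLT rule lets enrollment continue.

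What is at stake is the number of patients exposed before a pause when the true rate is unacceptable. Final detection by patient 20 is hardly affected. Any early checkpoint must be set against the final boundary, because the cost in false pauses depends on it, and section 6.2 leaves that boundary in doubt: its threshold and its printed probabilities do not match.

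**Working it through.** **Inputs from Protocol 6.2.** n = 20; pause at 7 or more DLTs; acceptable rate 25%, unacceptable rate 45%; printed probabilities 0.1018 (labelled 25%) and 0.7480 (labelled 30%). The 60% rate below is my addition, to show behaviour above the design range.

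**Step 1: the plan's own figures.** P(X ≥ r) = Σ over k = r to 20 of C(20,k) p^k (1−p)^(20−k).

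| Rule | 25% | 30% | 45% |
|---|---|---|---|
| 7 or more of 20 | 0.2142 | 0.3920 | 0.8701 |
| 8 or more of 20 | 0.1018 | 0.2277 | 0.7480 |

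The printed pair does not follow from the written rule. It is reproduced to four digits by 8 or more, at 25% and 45%. The printed 30% label fits neither row.

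**Step 2: the gap.** A count of 6 is below 7, so nothing is triggered.
- Six of six: 0.25^6 = 0.0002, 0.45^6 = 0.008, 0.60^6 = 0.047.
- Exactly six of ten at 45%: 210 × 0.45^6 × 0.55^4 = 210 × 0.008304 × 0.091506 = 0.160.
- Seven or more within ten patients at 45%, that is, the written rule has acted by then: 0.102.

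**Step 3: illustrative checkpoints.** Let s_n(k) be the probability of k DLTs after n patients with no pause so far. Then s_n(k) = s_(n−1)(k)(1−p) + s_(n−1)(k−1)p. After each patient, mass at or above the final boundary is moved to pause; at n = 6 and n = 10, mass at or above the checkpoint is moved too. Mean patients evaluated = Σ over n = 0 to 19 of Σ_k s_n(k), which counts 20 when no pause occurs. Outcomes are treated as known at once.

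| Final boundary | Checkpoints | Pause at 25% | Pause at 45% | Mean evaluated at 45% | Mean evaluated at 60% |
|---|---|---|---|---|---|
| 7 | none | 0.2142 | 0.8701 | 15.1 | 11.7 |
| 7 | 5 of 6 or 6 of 10 | 0.2155 | 0.8706 | 14.5 | 10.6 |
| 7 | 4 of 6 or 5 of 10 | 0.2349 | 0.8776 | 12.7 | 8.7 |
| 8 | none | 0.1018 | 0.7480 | 16.8 | 13.3 |
| 8 | 5 of 6 or 6 of 10 | 0.1067 | 0.7524 | 15.6 | 11.2 |
| 8 | 4 of 6 or 5 of 10 | 0.1447 | 0.7797 | 13.2 | 9.0 |

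Cost in false pauses at 25%:
- Milder set: 0.2155 − 0.2142 = 0.1 points (final 7) and 0.1067 − 0.1018 = 0.5 points (final 8).
- Stricter set: 0.2349 − 0.2142 = 2.1 points (final 7) and 0.1447 − 0.1018 = 4.3 points (final 8).

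**Step 4: when the false pauses fall.** With final boundary 7, the probability of a pause by patient 10 at 25% is 0.004 without checkpoints, 0.021 with the milder set and 0.089 with the stricter set.

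**Step 5: accrual lag.** This simulation assumes 4.5 patients a month (midpoint of section 6.3), DLT onset uniform over the 30 days and no accrual hold. The onset pattern is an assumption. With final boundary 7, mean patients enrolled at the pause (20 if none) goes from 16.8 to 16.1 (milder) or 14.2 (stricter) at 45%, and from 13.8 to 12.5 or 10.3 at 60%. The savings are of the same order as in step 3.

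**The case against.** The rule is coherent as a count: it acts at once on the seventh event and does not wait for patient 20. Nor is it the only oversight. Treatment-caused deaths have their own stop, which would act if at least five of six early DLTs were such deaths, and section 7.5 sends SAEs to the sponsor, ethics committee and regulators within 24 hours. This stands, but the death rule does not catch non-fatal DLTs, and SAE reporting does not pause enrollment.

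Early checkpoints also pause on thin data. The exact 95% intervals for 4 of 6 (22% to 96%) and 5 of 10 (19% to 81%) both contain the acceptable 25%. Since section 6.2 names only revision or termination after a suspension, a false early pause under the present text could be costly. Both points stand and shape the fix.

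Three stronger readings are tempting and are not supported:
- A reader might infer that checkpoints are almost free. That depends on the cut-offs and on the unsettled final boundary: the stricter set costs 2.1 points against 7 but 4.3 against 8.
- A reader might infer that 7 of 20 should simply be kept. The document cannot settle whether the threshold or the probabilities are in error.
- A reader might take "So far, there have been no prospective studies to confirm this scientific hypothesis" to mean that nothing is known about safety. The sentence concerns the efficacy hypothesis and clinical value of the triple combination. The background also reports radiotherapy with GM-CSF in 41 patients without dose reduction or interruption for toxicity.

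**Conclusion.** The point holds in a limited form. As written, section 6.2 has no DLT boundary before the seventh event, so six DLTs in six or in ten patients pause nothing. If 8 or more was intended, seven in seven would pause nothing either.

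Six of six is rare even at 45% (0.008) and only illustrates the gap. The practical gain is a modest average saving: about 0.6 to 2.4 patients evaluated at 45% with a final boundary of 7, or 16.8 − 15.6 = 1.2 to 16.8 − 13.2 = 3.6 from the rounded means with a final boundary of 8, and more with 7 at 60% (1.1 to 3.0). The price is slightly more, and earlier, false pauses at the acceptable rate.

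The mismatch between threshold and printed probabilities is certain and must be resolved first. The savings assume independent patients with a common DLT rate; the enrolled-patient figures also rest on the assumed onset pattern.

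**What to change.** 1. Reconcile the section 6.2 threshold with its printed probabilities and rate labels. The text does not show which was intended; the sponsor must say.
2. Add early enrollment-pause checkpoints calibrated to the reconciled boundary. The two sets above show the trade-off and are not a recommendation of particular cut-offs.
3. State that a checkpoint pause is a data review after which enrollment may resume unchanged, since section 6.2 now names only revision or termination.
4. Report the operating characteristics of the whole rule at 25% and 45%: pause probability, expected number treated and the chance of an early pause.

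The cost is protocol wording. DLTs are already monitored, and no extra patients or visits are needed. The downside to accept openly is the rise in false pauses at 25%: 0.1 to 0.5 points with the milder set and 2.1 to 4.3 points with the stricter one, depending on the final boundary, with some pauses coming by patient 10.
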